## Abstract

**Background:**

Muscles get smaller and weaker as we age and become more vulnerable to atrophy when physical activity is reduced or removed. This research is designed to investigate the potentially protective effects of two separate exercise strategies against loss in skeletal muscle function and size, and other key indices of health, following 14 days of reduced physical activity in older men.

**Methods:**

Three groups of 10 older men (aged 65–80 years) will undertake 2 weeks of reduced activity by decreasing daily steps from more than 3500 to less than 1500 (using pedometers to record step count). Two of the three groups will then undertake additional exercise interventions, either: 4 weeks of progressive resistance training prior to the step-reduction intervention (PT-group), or home-based ‘exercise snacking’ three times per day during the step-reduction intervention (ES-group). The third group undertaking only the step-reduction intervention (control) will provide a comparison against which to assess the effectiveness of the protective exercise strategies. Pre and post step-reduction assessments of muscle function, standing balance, anthropometry and muscle architecture will be taken. Pre and post step-reduction in postprandial metabolic control, resting systemic inflammation, adipose inflammation, oxidative stress, immune function, sleep quality, dietary habits, and quality of life will be measured. The stress response to exercise, and signalling protein and gene expression for muscle protein synthesis and breakdown following an acute bout of exercise will also be assessed pre and post step-reduction. Rates of muscle protein synthesis and adipose triglyceride turnover during the step-reduction intervention will be measured using stable isotope methodology. All participants will then undertake 2 weeks of supervised resistance training with the aim of regaining any deficit from baseline in muscle function and size.

**Discussion:**

This study aims to identify exercise strategies that could be implemented to protect against loss of muscle power during 2 weeks of reduced activity in older men, and to improve understanding of the way in which a short-term reduction in physical activity impacts upon muscle function and health.

**Trial registration:**

ClinicalTrials.gov: NCT02495727 (Initial registration: 25 June 2015)

## Background

The ageing process is accompanied by a progressive loss of muscle size and strength, and data from longitudinal studies suggests that muscle size is lost at 0.5–1 % per year after the age of 50 [1]. With ageing, muscle strength is lost two to five times more rapidly than would be expected based on the rate of muscle mass loss [2], and at twice the rate in the legs compared to the upper body [3]. Muscle power is the product of force and velocity of movement, and it is evident that power decreases with age to an even greater extent than strength [4]. Power provides an indication of the neuromuscular component of muscle function and thus is considered to be a better predictor of functional status than muscle mass or strength alone [5, 6]. Frailty is largely caused by this loss of muscle function [7, 8], eventually resulting in the tasks of daily living becoming too physically strenuous to be managed safely, and independent living becoming untenable.

Physical activity has been shown to be vitally important for maintaining muscle mass and function. During periods of dramatically reduced activity, such as bed rest, the muscles of healthy individuals rapidly lose size, strength and power, most notably from the legs [9, 10], with older individuals seemingly more vulnerable to this complete ‘disuse-induced’ muscle atrophy than younger individuals [11, 12]. In a population of generally healthy older individuals, however, extended periods of bed rest are unlikely to occur unless accompanied by severe injury or illness that may cause muscle wasting independently. Periods of reduced activity in healthy older adults are more likely to be the result of minor injury or illness, or extended bad weather [13, 14]. Scenarios such as these would result in a reduction in the number of steps walked on a daily basis for a short period of time, rather than total bed rest. The only previous investigation to focus on this step-reduction model of reduced physical activity in older people without any protective interventions demonstrated that reducing walking to less than 1500 steps per day for 2 weeks resulted in an average loss of around 4 % of leg muscle tissue, but with some participants losing up to 9 % [15]. In light of the estimated annual loss of 0.5–1 % of muscle size this much larger loss due to step-reduction is a concerning observation, particularly with periods of reduced activity occurring more often in older age [13]. However, in the aforementioned study, muscle strength was not reduced by the period of step-reduction, which is surprising given that strength is typically lost more rapidly than muscle size [16]. It should be noted that muscle strength was measured by assessing unilateral isometric knee extensor torque using a dynamometer for which extensive familiarisation has been demonstrated to be crucial to obtain reliable results [17]. Furthermore, changes in muscle power cannot be inferred from isometric dynamometry. Given that the nervous system is shown to adapt to changes in physical activity levels more rapidly than the contractile structures of muscle tissue [18], muscle power may be more sensitive to periods of reduced activity than maximum-force-producing capabilities. An additional and critically important role of the neuromuscular system is to maintain postural balance. If the neuromuscular system is compromised after a period of reduced activity it could be hypothesised that balance would be affected leading to an increased risk of falling [19, 20].

With only two studies previously investigating this topic specifically in an older population [15, 21], many questions remain as to the precise physiological mechanisms causing such marked response in muscle tissue to a seemingly benign and common scenario [22]. Although there is a wealth of literature highlighting the importance of maintaining physical activity for many elements of healthy ageing [23], relatively little direct evidence exists regarding the impact of acutely reducing activity in already healthy individuals. The physiological responses occurring when physical activity levels change are not confined to single tissues or organs [24], and it is crucial to understand the interactions between tissues that result in negative health outcomes such as muscle loss, particularly in an older population. Gaining an understanding of the impact of short-term reductions in physical activity is also a crucial precursory step to identifying protective interventions with real-world applicability. Resistance exercise is widely regarded to be the primary countermeasure against ‘disuse-induced’ muscle wasting [10, 25, 26]. In circumstances in which a period of reduced activity is scheduled but physical activity will subsequently be limited, for example, following to minor elective surgery, physical preparation through a concentrated period of resistance training may raise the ‘baseline’ muscle function and health profile such that reduced activity-induced muscle loss is compensated for. This may present a strategy to improve recovery from reduced activity as performance tasks of daily living should be no more challenging than prior to the pre-training, thus potentially allowing return to previous habitual activity levels more quickly.

There may of course be circumstances in which reduced activity is unavoidable but capacity to exercise is not compromised, for example, during extended inclement weather. Devries et al. [21] demonstrated that laboratory-based low-load resistance thrice weekly in fact increased leg lean tissue in older men during 2 weeks of step-reduction to less than 1500 steps/day. However, restricted access to resistance exercise equipment may render this exercise strategy infeasible; thus, home-based, body weight exercise may be a practical alternative to low-load resistance training. Previously, other health indices (e.g. metabolic health and mobility in frail older people) have been demonstrated to be improved by such exercise regimes [27, 28]. Again, this presents an opportunity to prevent decline in muscle function due to periods of reduced physical activity that may contribute to frailty, increased risk of falls, and their associated negative implications.

### Study objectives

The primary aim is to determine the protective effects of two exercise interventions against the loss of lower limb skeletal muscle power in healthy men aged 65–80 years undertaking 14 days of reduced physical activity (less than 1500 steps per day). The two exercise interventions are either: (1) undertaking 4 weeks of resistance training prior to the 14 days of step-reduction, or (2) home-based ‘exercise snacking’ during the 14 days of step-reduction. Alongside this, the influence of the step-reduction intervention and potential protective effects of the exercise interventions on other indices of muscle function (strength and neural drive), standing balance, anthropometric measures, metabolic health, rate of muscle protein and adipose triglyceride synthesis during ‘free-living’, markers of inflammation and oxidative stress at rest and in response to exercise, immune function (e.g. lymphocyte cytokine production), dietary habits, sleep quality and quality of life will be assessed. Thereafter, the possible benefits of the exercise interventions on recovery of muscle function and size will be investigated. Once all elements of the study are completed, the acceptability of the interventions and feasibility of adhering to the approaches of the recommended exercise strategies will be assessed, and user-generated input for improvements to future follow-on work obtained.

### Study design

The methods described herein have been approved by the National Health Service (NHS) South West Cornwall and Plymouth Research Ethics Committee (REC) with an allocated REC reference number: 15/SW/0130. The project was subsequently registered as a clinical trial (ClinicalTrials.gov: NCT02495727). The Standard Protocol Items: Recommendations for Interventional Trials (SPIRIT) checklist was completed.

The study will address the objectives by way of a three-group randomised control trial. One group will act as a ‘control’ against which to compare the potential protective effects of exercise interventions insofar as this group will undertake step-reduction without either exercise intervention. Hypotheses: (1) reduced activity alone will result in loss of leg muscle power, (2) exercise pre-training will increase leg muscle power above baseline so any loss of muscle power due to the reduced activity period will be offset to such an extent that muscle power will remain above pre-training baseline, and (3) daily exercise snacking during the reduced activity period will attenuate the decline in leg muscle power due to reduced activity.

## Methods

### Recruitment

The study will be advertised on the University of Bath web pages, and on posters placed around the University of Bath campus and distributed to local community clubs for older people in the Bath area. A press release will be sent to local newspapers and radio and television media outlining the study objectives and it is expected that interviews will be carried out as a result to raise awareness of the study.

### Inclusion criteria

In order to participate in this study, volunteers must satisfy all of the following criteria:Be aged 65 to 80 yearsNot be underweight or obese (body mass index (BMI) ≥20 and ≤30 kg/m^2^)Be a non-smoker (for more than 5 years)

### Exclusion criteria

Participants will not be able to take part in this study if they meet any one of the following criteria:Have any chronic illness, cardiac, pulmonary, liver, or kidney abnormalities, uncontrolled hypertension, peripheral arterial disease, insulin- or non-insulin dependent diabetes or other metabolic disordersAre individuals who consume on a daily basis any analgesic or anti-inflammatory drug(s), prescription or non-prescriptionAre individuals taking medications known to affect protein metabolism (i.e. corticosteroids, non-steroidal anti-inflammatory drugs, or prescription-strength acne medications)Are individuals with a history of bone, joint or neuromuscular problems or a current musculoskeletal injuryAre individuals with a known bleeding disorder, take the anticoagulant drug warfarin, or are prone to keloid scarringAre individuals with a known negative reaction to the local anaesthetic lidocaineAre individuals with any joint replacement surgical implants or other artefacts containing metalAre individuals who completed fewer than 3500 steps per day (as assessed by pedometer) prior to the studyAre individuals who score less than 8 on the Short Physical Performance Battery [29]

### Population and sample size

Thirty healthy men (non-smokers without diabetes) aged 65–80 years will be recruited and randomised into three groups of 10 by way of minimisation to limit between group differences in mean age, BMI and habitual steps/day. Participant and researcher blinding to group allocation is not possible, and screening and group allocation will be implement by the same researcher for all participants

The study is powered to detect the protective effect of the aforementioned exercise strategies against loss of leg muscle power during 14 days of reduced activity. Over 14 days of step-reduction a mean (SD) decrease of 3.9 (2.4 %) in lower limb muscle mass is anticipated [15], with measures of muscle power expected to decline at a similar or faster rate; thus, seven participants per group (95 % power and 5 % alpha) will be required to observe changes in leg muscle strength. The decline in muscle power is expected to be the same in the pre-training group as in the control group, hence significant increases in leg muscle power prior to reducing physical activity are required. Significant increases in leg strength in older men with 4 weeks of pre-training could be observed using nine participants (95 % power and 5 % alpha) [30], and it expected that this would be equivalent in muscle power. It is difficult to predict the extent of the protective effect likely to be provided by the exercise snacking. Therefore, the sample size will be rounded to 10 participants per group to account for drop out and the potentially more subtle changes that might be observed in the secondary measures.

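### The stated 95 % power belongs to within-group changes in muscle mass and strength, not to leg power or to protection between groups, which the trial says it is powered for

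*Protocol article*

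**What the plan says.** The section on population and sample size opens by stating that the study is powered for the protective effect of the exercise strategies on leg muscle power. The primary outcome, under Data analyses, is leg power: the change over step-reduction and the differences between groups.

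Two calculations follow.

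- **Step-reduction.** The input is "a mean (SD) decrease of 3.9 (2.4 %) in lower limb muscle mass is anticipated [15], with measures of muscle power expected to decline". One clause links mass to power, by assuming that power falls no more slowly than mass. The conclusion drawn is "seven participants per group (95 % power and 5 % alpha) will be required to observe changes in leg muscle strength".
- **Pre-training.** "Significant increases in leg strength in older men with 4 weeks of pre-training could be observed using nine participants (95 % power and 5 % alpha"), citing another study. The link to power is that "it expected that this would be equivalent in muscle power".

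The section says the snacking effect is hard to predict. It rounds to ten per group to cover drop-out and subtler changes in secondary measures. Under Statistical analyses, strength and power are to be compared before and after by paired t tests.

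The Background reports that in the step-reduction study supplying the mass figures, "muscle strength was not reduced by the period of step-reduction, which is surprising given that strength is typically lost more rapidly" than size.

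**The concern.** The first calculation takes its numbers from muscle mass, assumes a rate of decline for muscle power, and concludes on muscle strength. These are three different outcomes, and only power is primary. The assumption speaks to the mean decline. Statistical power depends on the mean divided by the SD of change, and nothing is said about the SD of change in a maximal-effort leg press test. The second calculation starts from strength and reaches power by expectation.

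The contrast also differs. Protection is a difference between an exercise arm and control, whereas the seven men, and apparently the nine, answer whether one group changes from before to after.

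If the wording stands, a null leg-power result could be read as coming from a trial with 95 % power to find an effect. The document does not establish that power.

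**Working it through.** **Inputs from the protocol (sample size section).** Mean fall 3.9 % and SD 2.4 %, both for lower limb muscle mass; alpha 5 %; power 95 %; seven men, nine men, and a final ten per group. Sidedness is not stated; two-sided is used below.

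**Method.** Noncentral t.
- Paired test: d = mean / SD, noncentrality d√n, n − 1 degrees of freedom.
- Two-sample test with n per arm: d = difference / SD, noncentrality d√(n/2), 2n − 2 degrees of freedom, with the same SD of change in both arms.

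**1. Reproducing the seven.** d = 3.9 / 2.4 = 1.625.
- Paired, n = 7: noncentrality 1.625 × √7 = 4.30; power 94.4 %. At n = 8 it is 97.4 %, and at n = 10 it is 99.5 %.
- Two-sample, n = 7 per arm: noncentrality 1.625 × √3.5 = 3.04; power 79.7 %. Reaching 95 % needs 11 per arm.

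The stated seven therefore fits a within-group paired calculation with the mass mean and mass SD used unchanged. The nine cannot be rebuilt in the same way, because the article gives no mean or SD for it; it is stated to be for strength.

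**2. The between-group contrast, still on the mass figures.** Take snacking against control.
- Complete protection, difference 3.9 %, d = 1.625: 80 % power at seven per arm; 93 % at ten (noncentrality 1.625 × √5 = 3.63).
- Half protection, difference 1.95 %, d = 0.8125: 41 % at ten per arm (noncentrality 1.82). Reaching 95 % needs 41 per arm.

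**3. What changes if leg power varies differently from mass.** The protocol gives no SD of change in leg power. The SDs and the larger means below are assumptions for illustration only.

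| Assumed mean fall | Assumed SD of change | d | Paired power, n = 10 |
|---|---|---|---|
| 3.9 % | 2.4 % (mass SD) | 1.625 | 99.5 % |
| 3.9 % | 4 % | 0.975 | 78 % |
| 3.9 % | 5 % | 0.78 | 60 % (59.5) |
| 3.9 % | 6 % | 0.65 | 45 % |
| 5 % | 4 % | 1.25 | 94 % |
| 6 % | 5 % | 1.20 | 92 % |
| 7 % | 6 % | 1.17 | 91 % |

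With the mean held at 3.9 %, paired power at ten men drops below 95 % once the SD exceeds about 3.0 %, and below 80 % once it exceeds about 3.9 %. The last three rows show that a faster mean decline, which the protocol allows for, would largely offset a larger SD.

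**4. What the group sizes can detect, without assuming any SD (80 % power, two-sided 5 %).**

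| Completers per arm | Within-arm change | Between-arm difference |
|---|---|---|
| 10 | 1.0 SD | 1.3 SD |
| 8 | 1.16 SD | 1.51 SD |
| 7 | 1.27 SD | 1.63 SD |

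**The case against.** The strongest defence is that the protocol discloses what it did. It names muscle mass as the input, states the link to power openly, and its arithmetic is right for the outcome it used. No passage says that leg power varies more than mass, and the assumed mean of 3.9 % is the lower edge of a similar or faster decline. All of this stands. It means that the size of any shortfall is unknown; it does not supply the missing SD or a between-group calculation.

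A reader might infer that the null strength result in the Background contradicts the assumed fall in power. The document does not support that. The same section discounts the result: it came from isometric torque, for which extensive familiarisation is described as crucial, and it is said to allow no inference about power. The section also argues that power may be more sensitive than maximal force. The trial itself uses a leg press test with two familiarisation sessions. The null result leaves the assumption untested and no more than that.

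A reader might also infer that the trial is underpowered by the amounts in the rows with SD 4 to 6 %. Those SDs are assumed, and the rows with larger mean falls point the other way.

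The rounding from seven and nine to ten could be offered as a margin. The section assigns it to drop-out and secondary measures, so it is not a stated allowance for a more variable primary outcome.

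Finally, lack of a detectable loss in the control arm would not empty every hypothesis. The pre-training hypothesis, that power stays above the pre-training baseline, could still be tested.

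**Conclusion.** The point holds as a mismatch between a claim and its inputs. The arithmetic is sound: seven men at 95 % is right, to within a point, for a within-group change in muscle mass. The opening claim is about leg power and protection, and neither 95 % figure is for that outcome or contrast.

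For leg power, the power of the trial is not established. With the mean at 3.9 % and an assumed SD of 4 to 6 %, paired power at ten men would be 78 % down to 45 %; a larger mean fall would offset this. The part that needs no assumed leg-power SD is the between-group result on the protocol's own mass figures: 80 % at seven per arm and 93 % at ten for complete protection, and 41 % at ten for half protection. It rests on two-sided testing and an equal SD of change in both arms. The correction is worth making and does not call the design itself into question.

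**What to change.** In the sample size section:

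1. State that the seven-man figure is a within-group calculation on muscle mass and the nine-man figure one on strength gains with pre-training, and that 95 % power is claimed neither for leg power nor for between-group protection.
2. Replace the reference to leg muscle strength in the step-reduction sentence with the outcome meant.
3. Give the effects detectable at 80 % power by number of completers, as in the last table under the working. Showing eight and seven as well as ten matters because the ten already includes the allowance for drop-out.

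The two familiarisation sessions should not be used to estimate the SD of change. Participants practise the power test there, so differences between sessions mix learning with test-retest noise and contain no variation in response to step-reduction. If such a figure is reported at all, it should be labelled test-retest variation.

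The cost is a few sentences and one small table, with no change to design, recruitment or measurements. The downside for the sponsor is that the stated power becomes less favourable.

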**Fig. 1 Fig1:**
[figure not shown]
A flow diagram of the study timeline. SPPB, Short Physical Performance Battery; BMI, bodymass index; PT-Group, pre-training group; ES-Group, exercise snacking group

### Preliminary screening

During an initial telephone contact initiated by potential participants, a member of the study team will provide a verbal overview of the study, and ask if the participant believes that they meet all of the inclusion criteria and none of the exclusion criteria. Those who are interested in participating will be sent information about the study requirements in writing. Interested participants will be asked to sign an informed consent form stating their willingness to undergo an eligibility screening with a member of the research team to ensure that participants do not exhibit any physiological condition that either poses undue personal risk or introduces bias into the experiment. During this screening, participants will undertake an objective assessment of physical function (Short Physical Performance Battery (SPPB) [29]). Only participants scoring over 7 out of 12 without scoring 0 on any element of the SPPB will be eligible to participate. Balance scales and a stadiometer will be used to determine the participant’s weight and height, recorded on inhalation of breath with the head positioned in the Frankfort plane position. BMI will subsequently be calculated. Participants will then be provided with a pedometer (CW600 Digi-Walker, Yamax, Tokyo, Japan) and instructed in its use, a physical activity monitor BodyMedia armband (Sensewear Professional 8.0, Pittsburg, PA, USA) and dietary record sheets. Participants will be asked to wear the pedometer and the BodyMedia armband for 7 days and to weigh and record all food and drink consumed for 3 days (including one weekend day) using a diet record sheet. The pedometer will record the daily step count and the reset step count at midnight each day. Only individuals who average 3500 steps per day or above will be invited to take part in the rest of the study, and at this point one of the investigators will describe the study verbally to them again and provide the opportunity for potential participants to gain clarification on any aspect of the study. Eligible participants will be randomly allocated to an experimental group by minimisation to limit difference in mean age, steps/day and BMI at baseline between groups. All further details of the elements of the study specific to the group will be provided. Written informed consent will be acquired at this stage in regard to each participant’s understanding and willingness to take part in the rest of the study after group allocation. The investigator will also explain to the participants that they are completely free to withdraw from the study at any time without any repercussions.

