### Exercise interventions

#### Pre-training group (PT)

The PT-group will attend 10 resistance training sessions across 4 weeks prior to the 14-day step-reduction, with sessions separated by at least 48 hours arranged at the participant’s convenience. The last training session will take place at least 3 but less than 7 days before the first main trial prior to step-reduction. All exercise sessions will be fully supervised by a member of the research team. Participants will complete the standardised warm-up on the Keiser leg press as performed during the familiarisation session. All training sessions will begin with leg press and leg extension, then alternate between two sessions (A and B) to incorporate variation into the programme (see Table 1). At the beginning of the fifth session, participants will repeat the 1RM and incremental power tests so exercise resistances can be adjusted to strength gains accordingly. Repetitions will be performed at a cadence of 1:1 for concentric-eccentric time, at a comfortable participant-selected pace that should be less than 5 s per complete repetition. Rest intervals between sets will be 90 to 120 s at the participant’s discretion.

**Table 1 Tab1:** Training session content and progression

Exercise		Sessions 1 and 2			Session 3–10		
Session A	Session B	Sets	Reps	Load	Sets	Reps	Load
Seated leg press		3	8	60 % 1RM	4	8	75 % 1RM
Seated leg extension							
DB calf raise	DB lat raise	2	10	70 % 10RM	3	10	80 % 10RM
DB bicep curl and press	RB seated row						

*1RM* maximum load at which a single repetition can be completed, *10RM* maximum load at which 10 repetitions can be completed, *DB* dumbbells, *Lat* lateral plane of motion, *RB* elastic resistance band, *Reps* repetitions

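### Written consent to the main study is taken after men learn their group, and one unblinded researcher both screens and allocates, so refusal could differ by arm

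*Protocol article*

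**What the plan says.** The Preliminary screening section of the Protocol article sets out a sequence. Men first "sign an informed consent form stating their willingness to undergo an eligibility screening". Screening covers the SPPB, BMI and a 7-day step count. Men who pass have the study described to them again and can ask questions. Next: "Eligible participants will be randomly allocated to an experimental group by minimisation". Then: "All further details of the elements of the study specific to the group will be provided". Written informed consent comes last, and concerns each man's understanding and his "willingness to take part in the rest of the study after group allocation".

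Population and sample size adds two facts. One is that "Participant and researcher blinding to group allocation is not possible". The other is that "screening and group allocation will be implement by the same researcher for all participants". The allocation is done "by way of minimisation to limit between group differences in mean age, BMI and habitual steps/day".

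The arms ask for different extra effort:
- **PT:** "The PT-group will attend 10 resistance training sessions across 4 weeks prior to the 14-day step-reduction", all supervised (Pre-training group).
- **ES:** home exercise three times a day during the 14 days of step-reduction (Exercise snacking regime).
- **Control:** step-reduction with neither exercise intervention (Study design).

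**The concern.** Randomisation makes the arms comparable at the moment of allocation. Here a man commits to the main study only after that moment, knowing what his arm will ask of him. If the men who withdraw at this step differ between arms in motivation, fitness or likely adherence, the men who start are no longer a random split of those allocated. Minimisation on age, BMI and steps per day does not address willingness to train, and it acts before refusal, not after.

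The shared role is a second, smaller route. The person who judges eligibility is also the person who allocates, and knows each man's age, BMI and step count from screening. Good practice keeps these two tasks apart.

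The primary outcome is the pre-to-post change in leg power and its difference between groups (Primary outcome measure), with 10 men per arm. In groups this small, one or two selective refusals can move an arm mean.

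**Working it through.** **1. Order of steps.** Could the consent phrase merely describe the part of the study that follows allocation, and not the timing of consent? The grammar of the phrase allows this, but the paragraph does not. Written consent is placed at the stage reached after allocation and after the group-specific details. The only earlier consent is limited to screening. No other section moves full-study consent forward.

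**2. What is known about a man who refuses.** Before allocation the plan collects SPPB, weight and height, step count, activity-monitor data and a diet record. The leg-press power test first appears under Familiarisation sessions, after allocation and consent. A man who declines on learning his arm therefore has no leg-power value, and his loss cannot be adjusted for with outcome data.

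**3. Scope for judgement at screening.** Age, BMI, SPPB and the 3500-step threshold are measured cut-offs. Some exclusions are not: any chronic illness, a history of bone, joint or neuromuscular problems, and the screener's check for conditions that could introduce bias. Some discretion remains with the person who also allocates.

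**4. Scale (illustration only).** The documents give no refusal data. The sample size section supplies a scale: an anticipated decline of 3.9 % with SD 2.4 %, measured on lower-limb muscle mass and used there as a stand-in for power. As a check on those inputs, d = 3.9/2.4 = 1.625. A two-sided 5 % paired t test with n = 7 then has 94.4 % power, close to the stated 95 %. This point does not depend on that figure.

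Assumptions:
- 10 men start in the affected arm after r extra men refuse.
- The r refusers are the least willing of the 10 + r allocated.
- Willingness correlates ρ with change in the outcome.

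The shift in the arm mean, in SD of change, is ρ × S_r / 10. S_r is the sum of the absolute expected values of the r smallest of 10 + r standard normal values.

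| r of 10 + r | S_r / 10 (ρ = 1) | ρ = 0.3 | ρ = 0.5 |
|---|---|---|---|
| 1 of 11 | 0.158 | 0.049 | 0.078 |
| 2 of 12 | 0.275 | 0.082 | 0.137 |
| 3 of 13 | 0.368 | 0.111 | 0.185 |

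The table entries are simulated. The exact formula agrees to within 0.002 (for example 0.5 × 0.368 = 0.184).

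- For ρ of 0.3 to 0.5 the shift is about 0.05 to 0.19 SD. Multiplying the unrounded values by 2.4 gives 0.118 to 0.445 percentage points, which is 3 % to 11 % of the 3.9 % decline.
- The extreme ρ = 1 gives 0.158 to 0.368 SD, or 0.38 to 0.88 points (10 % to 23 % of 3.9 %).
- For comparison, the standard error of a difference between two arms of 10 is √(2/10) = 0.447 SD. The range for ρ of 0.3 to 0.5 is 0.049/0.447 = 11 % to 0.185/0.447 = 41 % of that standard error.

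**The case against.** **Information before allocation.** Men get a telephone overview, written study requirements and a second verbal description before they are allocated. Many who dislike the study would leave then. This stands as a mitigation. It does not stop a man from declining because of the particular arm he draws.

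**Shared burden.** All arms undergo two main-trial days with biopsies, resting biopsies on days 3, 8 and 18, step restriction and six re-training sessions. Against that load, the effect of arm on refusal may be small. This is fair, and the effect is unknown. The 10 extra PT sessions are still a real difference, and they come first in that arm's timeline.

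**Objective gates.** The main entry criteria are measured, which limits selection by the screener. This too stands, subject to the medical-history exclusions noted in the working.

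Three stronger readings are tempting, and the documents support none of them:
- *The researcher can foresee the next assignment.* The article says allocation is random by minimisation. It does not say whether there is a random component or how assignments are released. An article commonly leaves such detail to the full protocol, so its silence is not evidence of predictability.
- *Comparability is broken.* No refusals are reported, so the documents show a possibility and not an event.
- *A baseline shift measures the harm.* If 2 of 12 men refuse and each lies 1 SD below the overall mean, the other 10 average 2/10 = +0.2 SD at baseline. The arithmetic is right, but the primary outcome is change, and a baseline shift does not carry over one for one.

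**Conclusion.** The point holds in a conditional form. The order of consent and the shared screening and allocation role are stated outright, and nothing elsewhere in the article repairs them. With unequal added burden, refusal after disclosure could differ by arm, and refusers would have no leg-power data. The direction and size of any bias are unknown. The range of about 0.05 to 0.19 SD in one arm's mean change rests on assumed refusal counts and correlations, and its conversion to percentage points rests on the plan's muscle-mass SD. On those inputs the shift is smaller than the random error of a between-arm comparison. It is nevertheless systematic and avoidable at little cost. The change should be made while recruitment continues (Trial status). The point does not by itself invalidate the trial.

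**What to change.** - For men not yet allocated, obtain written consent to the whole study, covering all three arms, once eligibility is confirmed and before allocation. Disclose the arm only afterwards.
- Have an existing team member who does not screen run and release the allocation once eligibility has been recorded.
- Report the number of men who decline after allocation, by arm, including those already allocated under the current order.

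Cost: a minor ethics amendment to the order of consent, using existing staff. Interventions, assessments and sample size do not change. The downside is that some men may decline before allocation instead of after it. That could slow recruitment slightly, but those refusals could not depend on the assigned arm.
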